# Acupuncture for patients with mild hypertension: study protocol of an open-label multicenter randomized controlled trial

**DOI:** 10.1186/1745-6215-14-380

**Published:** 2013-11-11

**Keywords:** Essential hypertension, Acupuncture, Acupoint specificity, Acupoints effect, Randomized controlled trials, Protocol

## Abstract

**Background:**

Several studies using acupuncture to treat essential hypertension have been carried out. However, whether acupuncture is efficacious for hypertension is still controversial. Therefore, this trial aims to evaluate the efficacy and safety of acupuncture for patients with mild hypertension.

**Methods/Design:**

This is a large scale, open-label, multicenter, randomized controlled clinical trial with four parallel arms. We will recruit 428 hypertensive patients with systolic blood pressure (SBP) between 140 and 159 mmHg, diastolic blood pressure (DBP) between 90 and 99 mmHg. The participants will be randomly assigned to four different groups (three acupuncture groups and one waiting list group) (1).The affected meridian acupuncture group (*n* = 107) is treated with acupoints on the affected meridians (2).The non-affected meridian acupuncture group (*n* = 107) is treated with acupoints on the non-affected meridians (3).The invasive sham acupuncture group (*n* = 107) is provided with sham acupoints treatment (4).The waiting-list group (*n* = 107) is not offered any intervention until they complete the trial. Each patient allocated to acupuncture groups will receive 18 sessions of acupuncture treatment over 6 weeks. This trial will be conducted in 11 hospitals in China. The primary endpoint is the change in average 24-hSBP before and 6 weeks after randomization. The secondary endpoints are average SBP and average DBP during the daytime and night-time, and 36-Item Short Form Survey (SF-36), and so on.

**Discussion:**

This is the first large scale, multicenter, randomized, sham controlled trial of acupuncture for essential hypertension in China. It may clarify the efficacy of acupuncture as a treatment for mild hypertension.

**Trial registration:**

Clinicaltrials.gov Identifier: NCT01701726

## Background

Essential hypertension continues to be an important public-health challenge worldwide [1]. Hypertension is an independent risk factor for premature death, heart disease, stroke, peripheral vascular disease, and renal failure. Hypertension affects 29.3% of the adult population in the United States [2]. In 2009,the direct and indirect costs for hypertension in the United States are projected to be approximately $73.4 billion [3]. In the fourth National Nutrition and Health Survey in 2002, the prevalence of hypertension among Chinese population was 18.8% [4], affecting approximately 200 million individuals in China, while mild hypertension accounts for >60% [5]. Furthermore, the number of hypertensive patients is still increasing [6]. It is also reported that in China, the direct medical costs for hypertensive patientsaged 35 to 75 years are ¥20.2 billion [7].

Pharmacological treatment remains the chief treatment option for mild hypertension. However, a recent Cochrane review found that there is no proved benefit in antihypertensive drugs treatment for patients with mild hypertension. In addition, owing to adverse effects of antihypertensive drugs, 9% of patients discontinue their treatment [8]. Non-pharmacological interventions including acupuncture prevail as a treatment option for hypertensive patients [9]. In China, acupuncture has been used to treat disease for >2,500 years, and it is also widely used all around the world. Nowadays, acupuncture is used to treat cardiovascular disease (such as angina pectoris [10], hypertension [11]). Several randomized controlled trials of acupuncture to treat hypertension had been conducted, but the results were not consistent. Therefore, we designed a multicenter randomized controlled trial to confirm whether acupuncture is efficacious and safe for hypertension.

In this trial, we first intend to investigate the efficacy of acupuncture to lower the blood pressure comparing the waiting-list control and invasive sham acupuncture groups. Second, we attempt to determine whether there is a difference between acupoints on the affected meridians according to meridian syndrome differentiation and the acupoints on the non-affected meridians. This clinical trial is financed by the national basic research program (973program) in China, and is registered with an identifier (http://NCT01701726) by clinicaltrials.gov in the USA.

## Methods/Design

### Design

This trial is an open-label multicenter randomized controlled trial with four parallel arms. We compare the affected meridians with non-affected meridians, sham acupuncture and waiting-list groups as well. The trial is performed in the following Hospitals: First Affiliated Hospital of Chengdu University of Traditional Chinese Medicine; Third Affiliated Hospital of Chengdu University of Traditional Chinese Medicine (TCM); Affiliated Hospital of Ningxia Medicine University; First Affiliated Hospital of Hunan University of TCM; Second Affiliated Hospital of Hunan University of TCM; Affiliated Hospital of Hunan University of TCM - Hengyang Hospital; Chenzhou No.1 People’s Hospital; First Affiliated Hospital of Guiyang College of TCM; Second Affiliated Hospital of Guiyang College of TCM; Yunnan Provincial Hospital of TCM; and Second Affiliated Hospital of Shanxi College of TCM.

The whole study period is 13 weeks,with a 1-week run-in period, 6-week treatment phase, and 6-week follow-up phase. After randomization, patients in acupuncture groups will receive 18 sessions of treatment over a 6-week treatment period. Participants in the waiting-list control group will give an option to receive acupuncture treatment after 13 weeks study period. Outcome measurements will be assessed at day 0, 6 weeks, 9 weeks, and 12 weeks after randomization. All patients will be informed that they may be randomly allocated to affected meridian acupuncture group, non-affected acupuncture group, invasive sham acupuncture group, or waiting-list group (Figure 1, Table 1). This trial will be conducted according to the principles of the Declaration of Helsinki (version Edinburgh 2000). The trial protocol has been approved by the regional ethical review committee of traditional Chinese medicine in Sichuan Province on April 2012. We will require all patients to sign the written informed consent, and they will be given enough time to decide whether they will take part in this trial. This trial started in September 2012, and will be completed in December 2017.

**Figure 1 F1:**
[figure not shown]
Trial flow chart.

**Table 1 T1:** Time to visit and data collection

	**-1 week**	**0 week**	**3 weeks**	**6 weeks**	**3 weeks after treatment**	**6 weeks after treatment**
	Baseline	Treatment phase			Follow-up phase	
**Patients**	X					
Informed consent	x					
Medical history	x					
Physical examination		x				
Randomization						
**Intervention**						
Affected meridian acupuncture group (*n* = 107)		18 sessions of acupuncture at acupoints				
Non-affected meridian acupuncture group (*n* = 107)						
**Comparisons**						
Incasive sham acupuncture group (*n* = 107)		18 sessions of acupuncture at non-acupoints				
Waiting-list group (*n* = 107)		18 sessions of treatment at the end of the trial				
**Outcomes**						
24-h blood pressure		x		x	x	x
Expectation of acupuncture		x				
SF- 36		x		x		
Response to treatment				x		
**Participants safety**						
Laboratory test		x				
Adverse events		x	x	x	x	x

SAS, Self-Rating Anxiety Scale; SDS, Self-Rating Depression Scale; SF-36, MOS item Short Form health survey.

### Randomization

Randomization is conducted by the third party (the Brightech Magnsoft Data Services Company) using text messages or a website. If the randomization succeeds, the investigators will receive an email confirmation. The randomization sequence (blocked, stratified for centers) is generated through the randomization module of the synthesized management platform of the Brightech Magnsoft Data Services Company (block length is unknown to centers). This procedure ensures each eligible patient having an equal probability of being assigned to four different groups, which will not be influenced by the researchers.

### Participants

Patients who meet the inclusion criteria will be included in this study. The criteria are as follows: (1) men or women aged between 40 and 75 years,; (2) participants meet the diagnostic criteria of mild hypertension according to JNC-7 [12] and 2010 Chinese guidelines for the management of hypertension [5](diagnosed as mild hypertension systolic blood pressure (SBP) 140–159 and/or diastolic blood pressure (DBP) 90–99 ,according to WHO/ISH criteria stage I); (3) patients who are initially diagnosed as mild hypertension or have been diagnosed as mild hypertension before, without taking any antihypertensive drugs; (4) patients who are diagnosed as Jue-yin syndrome (yin-deficiency accompany with hyperactivity of yang) or Yang-ming syndrome (obstruction of phlegm and dampness) according to meridian syndrome differentiation; (5) patients who are willing to comply with our study protocol; (6) participants agree to sign informed consent form.

The exclusion criteria are as follows: (1) patients who have been diagnosed with secondary hypertension [13] or malignant hypertension (for example, Cushing’s syndrome, coarctation of the aorta, pheochromocytoma, renal parenchymal disease, primary aldosteronism, renovascular hypertension, obstructive sleep apnea, drug-induced hypertension, and so on); (2) patients accompanied with other severe medical conditions (for example, endocrine disorders, cardiovascular disease, digestive disease, hepatic dysfunction, cerebral vascular disease, renal disease, hematologic disease,and so on); (3) patients with a chronic disease (for example, epilepsy, severe depression, or anxiety (SAS ≥70, SDS ≥70), psychosis, allergic constitution, accompany with any infection), pregnant women or women in lactation or women of childbearing potential planning to conceive in the next 6 months; (4) patients who currently participate in another clinical trial; (5) patients who had been treated with acupuncture during the previous 3 months. If one of the criteria mentioned above is matched, the participant will be excluded.

During the whole study period, participants will not be hospitalized, taking into account: (1) we only recruit patients with mild essential hypertension who went off hypertensive drugs and without complications; (2) we could observe the blood pressure of participants under regular activities; (3) patients with mild essential hypertension are not appropriate to recruit for inpatient treatment.

#### **
*Recruitment strategies*
**

We will apply two strategies to recruit participants with mild hypertension. First, we recruit participants from outpatient clinics of the participated hospitals. Second, we employ three kinds of advertisements to attract patients to join our study. We will distribute printed recruitment posters in the participated hospitals and the communities nearby. Meanwhile we will publish advertisement in local newspaper and broadcast television advertisements on the local channel.

#### **
*Intervention*
**

##### 

**Rationale for selection of acupoints** According to TCM theory, hypertension pertains to the coverage of vertigo and headache. Based on previous survey and expert consultation, Jue-yin syndrome (yin deficiency with yang hyperactivity) and Yang-ming syndrome (the obstruction of phlegm and dampness) are the most common syndromes in mild hypertension. Therefore, in accordance with meridian syndrome differentiation, we select acupoints on the Yang-ming, Jue-yin, and Shao-yin meridians. Hence, it is reasonable that the acupoints on the affected meridians would be most effective at treating mild hypertensive patients. Meanwhile we also choose acupoints on the non-affected meridians (Gallbladder, San-jiao, and Spleen meridians) which were reported to be useful to decrease blood pressure according to our previous literature research.

In our trial, there are four groups: (1) affected meridian group;(2) non-affected meridian group;(3) sham acupuncture group;and (4) waiting-list group (Table 2). Apart from the waiting-list group, the other patients assigned to the three acupuncture groups will each receive 18 sessions of acupuncture treatment.

1. Affected meridian acupuncture (AMA)

Participants in the affected meridian group (Figure 2) are treated according to two syndromes (Jue-yin syndrome and Yang-ming syndrome). Jue-yin syndrome: taichong (LR3), renying (ST9), taixi (KI3), and neiguan (PC6) are punctured with filiform needles bilaterally. Taichong (LR3) is punctured perpendicularly 0.5-1.0 cun. Renying (ST9) is punctured perpendicularly 0.3-0.8 cun, paying attention to avoiding the carotid artery. Taixi (KI3) is punctured perpendicularly 0.5-1.5 cun. Neiguan (PC6) is punctured perpendicularly 0.5-1.0 cun. Yang-ming syndrome: taichong (LR3), renying (ST9), zusanli (ST36), and quchi (LI11) are punctured with filiform needles bilaterally. Taichong (LR3) is punctured perpendicularly 0.5-1.0 cun. Renying (ST9) is punctured perpendicularly 0.3-0.8 cun, paying attention to avoiding the carotid artery. Zusanli (ST36) is punctured perpendicularly 1.0-2.0 cun. Quchi (LI11) is punctured perpendicularly 1.0-1.5 cun.

After insertion, all the acupoints will be manually stimulated by lifting and thrusting associated with twirling and rotating the needle, to elicit 'de-qi’. Jue-yin syndrome and Yang-ming syndrome will be identified by the practitioner according to the diagnostic characteristic variables of TCM (Table 3).

2. Non-affected meridian acupuncture (NMA)

Fengchi (GB20), waiguan(SJ5), yinlingquan(SP9), and xuehai (SP10) are punctured by filiform needles bilaterally (Figure 3). Fengchi (GB20) is punctured obliquely 0.8-1.2cun, with the tip of the needle pointing to the apex of nose. Waiguan (SJ5) is punctured perpendicularly 0.5-1.0 cun. Yinlingquan (SP9) is punctured perpendicularly 1.0-2.0 cun. Xuehai (SP10) is punctured perpendicularly 1.0-1.5cun. All the acupoint locations are in accordance with the WHO Guideline for Acupuncture Point Locations [14].

After insertion, all the acupoints will be manually stimulated by lifting and thrusting associated with twirling and rotating the needle, to search for 'de-qi’.

3. Invasive sham acupuncture (ISA)

Sham acupoints (Figure 4):

(1) The edge of the tibia (1–2 cm lateral and horizontal to the zusanli (ST36))

(1) Halfway between the tip of the elbow and the axilla

(1) On the ulnar side of the arm, halfway between the epicondylus medialis of the humerus and the ulnar side of the wrist

(1) 2 cm superior to fu tu (LI18)

We use pre-validated sham acupoints [15]. After the insertion, we will not use any manipulationand 'de-qi’ sensation is not needed.

4. Waiting-list (WL)

Participants in the WL group will not be treated throughout 13-week observation period. And they will be required to maintain their current lifestyle, including diet and exercise. At the end of trial, if the participant would like to be treated with acupuncture, we will offer acupuncture treatment three times weekly for 6 weeks.

**Table 2 T2:** Details of acupuncture protocol

AMA	Jue-yin syndrome	Taichong (LR3), renying(ST9), taixi(KI3), neiguan(PC6)
	Yan-ming syndrome	Taichong (LR3), renying(ST9), zusanli(ST36), quchi(LI11)
NMA		Fengchi(GB20), waiguan(SJ5), yinlingquan(SP9), xuehai(SP10)
ISA		1. The edge of the tibia (1–2 cm lateral and horizontal to the zusanli (ST36))
		2. Halfway between the tip of the elbow and the axilla
		3. On the ulnar side of the arm, halfway between the epicondylus medialis of the humerus and the ulnar side of the wrist
		4. 2 cm superior to futu(LI18)

AMA, Affected meridian acupuncture group; ISA, Invasive sham acupuncture group; NMA, Non-affected meridian acupuncture group.

**Figure 2 F2:**
[figure not shown]
Locations of acupoints: affected meridian acupuncture group (AMA).

**Table 3 T3:** Diagnostic characteristic variables of TCM

	**Yin deficiency with yang hyperactivity**	**Obstruction of phlegm and dampness**
Pulse	Wiry, thin,fast	Slippery and soggy
Tongue	Red with no coating, peeled	Greasy coating, swollen
Other primary symptoms	Vertigo, headache, malar flush, both knee and loin feel sore and weak, dysphora in chest, palms, and soles, irritable, dry mouth, dry eyes, palpitation, insomnia, poor memory	Heavy head and or body, muddled thinking, overweight, vertigo, palpitation, poor appetite, nausea, stuffy feeling in the chest and/or epigastrum, heavy frontal headache, insomnia
Secondary symptoms	Concentrated dark urine, dry stools, blurred vision, numbness and tremors of limbs, tinnitus	Tinnitus, numbness in the limbs, loose stools

**Figure 3 F3:**
[figure not shown]
Locations of acupoints: non-affected meridian acupuncture group (NMA).

**Figure 4 F4:**
[figure not shown]
Locations of non-acupoints: invasive sham acupuncture group (ISA).

During the whole study period, all the participants are not allowed to take any medical treatment for lowering blood pressure; drugs, herbs, and physical therapy are forbidden. If the participants suffer from other diseases and need to be treated with drugs,they have to record the drugs they take, and measure their blood pressure after drugs, all of which will be recorded in the case report forms.

In each session, acupuncture is applied bilaterally. After insertion, apart from the acupoints around the neck (ST9, GB20, non-acupoints4), six auxiliary needles will be punctured at 2 mm lateral to each acupoint or non-acupoint. As to the auxiliary needle, we will not do any manipulation. We use transcutaneous electric acupoints stimulation (HANS; Han’s acupoints nerve stimulator, HANS-200, Nanjing, China) to stimulate the acupoints and non-acupoints. Except for the acupoints around the neck (ST9, GB20, non-acupoints 4), the other acupoints or non-acupoints and their auxiliary needles are connected with electricity by HANS for 30 min, the frequency is 2HZ, and the intensity is confined to 2 mA. It had been demonstrated that 30 min of low-frequency electro-acupuncture activates opioid receptors and provides a therapeutic effect on hypertension [16,17].

The treatment will be performed after sterilizing the skin with 75% alcohol on the areas where the needles will be inserted, and with the patient lying in the supine position. We use two types of Hwato disposable steel needles (Suzhou Hua Tuo Medical Instuments, Suzhou, China): length 25–40 mm, diameter 0.25 mm; and length 13 mm, diameter 0.18 mm. All the groups but the patients in waiting-list group are asked to retain the needles for 30 min.

Apart from waiting-list group, the patients from the other groups will receive 18 sessions of acupuncture treatment over 6 weeks, three times per week. During the whole observation period, no patients are allowed to take antihypertensive drugs.

#### **
*Outcome measurement*
**

##### 

**Primary endpoint** The primary outcome measurement in this study is the change in average 24-hSBP and DBP before randomization and 6 weeks after randomization. Ambulatory mean blood pressure (ABPM) is superior to clinic BP in the prediction of cardiovascular morbidity and mortality [18,19]. Because ABPM exerts a different predictive effect on the cardiac and cerebrovascular complications [20] we selected ABPM as our primary endpoint.

##### 

**Secondary outcome measures** Ambulatory pulse pressure (APP) [21] is a well-established marker of cardiovascular risk. We choose APP as one of the secondary endpoints to evaluate the effect of acupuncture for hypertension. There is a prospective study [22] that shows that both high ABPM values and abnormal daytime/night-time BP profiles are associated with later occurrence of ischemic cerebrovascular and coronary events independently of casual BP values and other cardiovascular risk factors. It is therefore necessary to observe the daytime/night-time BP of hypertensive patients.

Changes in patients’ health-related quality of life, according to the SF-36 (Medical Outcomes Study 36-Item Short Form) questionnaire Chinese version is another secondary outcome measure [23]. The validity and reliability of this scale have proven in previous studies [24,25]. The scale contains eight dimensions (physical function, role physical, bodily pain, general health, vitality, social function, role emotional, mental health) and two summary components (physical and mental), measured on a scale of 0 to 100. Lower scores indicate a poorer quality of life. SF-36 investigates at 0 day and 6 weeks after randomization.

Response to the treatment will be measured at the end of treatment, using a five-point Likert self-administered scale:'Compared with pre-treatment, to what extend did you think your hypertensive symptoms change?’1, absence of all symptoms; 2, significantly improved; 3, moderately improved; 4, not changed; 5, deteriorated. 'After treatment, how do you evaluate the effect of acupuncture for hypertension?’ 1, no effect(0%); 2, a little effect(25%); 3, moderate effect(50%); 4, a significant effect (75%); 5, complete response(100%). The patients fill in this questionnaire at the end of the treatment.

Expectation of the treatment will be measured by a self-administered questionnaire. With seven items as follows: (1) In the coming year, how will you think your disease will be relieved? (significantly(≥75%); moderately(approximately 50% to 75%); a little(approximately 25% to 50%); no change(0% to 25%)); (2) How effective do you think acupuncture is for hypertension? (significant(≥75%); moderate(approximately 50% to 75%); a little(approximately 25% to 50%); no change(approximately 0% to 25%)); (3) Which treatment options do you prefer to take as your treatment for hypertension? (acupuncture and moxibustion; herbs; Western medicine; others); (4) How familiar are you with acupuncture and moxibustion? (very familiar; so-so; a little; not at all); (5) By what means did you get to know about acupuncture and moxibustion? (friends and relatives; media reports; medical work; others); (6) How did acupuncture and moxibustion work in your memory? (excellent; good; so-so; not at all); (7) During the treatment, are you afraid of the pain or uncomfortable sensation caused by acupuncture and moxibustion? (very much; a little; never think about it; feel comfortable). The subjects will mark the best answer for each of the questions. The assessment will be performed at day 0 after randomization.

Before randomization, a special pattern identification questionnaire was developed to differentiate which syndrome the subjects pertaining to.

#### **
*Blood pressure measurement*
**

Ambulatory blood pressure measurements are performed with an oscillometric device (A&D Co.Ltd., Japan TM-2430). During a 24-h monitoring period, the device takes 76 measurements. Daytime is defined as 08:00–22:00. The measurement during the daytime will be taken every 15 min. Night-time is defined as 22:00–08:00. The measurement during the night-time will be taken every 30 min. The 24-h ambulatory blood pressure monitoring measures at baseline, 6 weeks, 9 weeks, and 12 weeks after randomization. Clinical blood pressure measurements will be taken before and after each acupuncture session with Automatic Upper Arm Blood Pressure Monitor (Omron HEM 7200, Liaoning, China).

#### **
*Participant safety*
**

Before randomization, all participants will undergo routine tests of blood, urine, stool sample, electrocardiogram examination, Doppler echocardiography, carotid ultrasonography, as well as blood biochemical tests (AST, ALT, BUN, Scr, fasting glucose, triglyceride, HDL cholesterol, LDL cholesterol, albumin/creatinine.). These tests will help identify and exclude participants with serious illnesses of the heart, liver, and kidneys, or other severe diseases.

Adverse events are defined as any unexpected or uncomfortable signs, symptoms, or diseases, regardless of the intervention. These adverse events include bleeding, hematoma, fainting, serious pain, and local infection. If any adverse events happen during the entire observation period, all the details should be documented in the case report form.

We have designed a case reported form containing a variety of information, and this will be completed by the corresponding researchers at each center. At each center, the obtained information will be recorded on an electronic database, for subsequent statistical analysis. During the observation period, if there are any drop-outs or withdrawals, the investigator must find out their reasons and record them in the case report form. The patients’ compliance during the 6 weeks of treatment and 6 weeks of follow-up will also be documented.

#### **
*Sample size calculation and statistical analysis*
**

According to the previous literature [26], the average 24-hSBP of hypertensive patients rose 1.6 mmHg after being treated by sham acupuncture, while the average 24-hSBP of hypertensive patients lowered 5.4 mmHg after being treated with verum acupuncture. Therefore, the adjusted mean difference between the two groups was 7 mmHg. In this study, we anticipated an 12 mmHg improvement by affected meridian acupuncture; 10 mmHg by non-affected meridian acupuncture; 3 mmHg by sham acupuncture; and 0 mmHg in the waiting-list group. The standard deviation is set as 20. We calculated this using 90% power at a 5% significance level with G*Power (version 3.1.2, Franz Faul, Universität Kiel, Germany), and the result showed an estimated 93 patients per group. Considering a drop-out rate of 15%, we plan to enroll 107 patients per group, 428 patients in total for the four different groups.

Statistical analysis protocol was designed by the Brightech-Magnsoft Data Services Company and principal investigators. Analysis of all data in this trial will be performed by the Brightech-Magnsoft Data Services Company. The data will be analyzed with SAS 9.1 and SPSS13.0 software packages. All analyses will be on the basis of the intention-to-treat (ITT) population and per-protocol (PP) population. The result of the ITT analysis will be compared with that of the PP analysis to determine whether the results are consistent. Missing data will be filled by Last Observation Carry Forward rules.

Demographic characteristics and other baseline values will be described using descriptive statistics for each group. For the primary outcome, we will run a comparison between pooled acupuncture groups and waiting list control group to figure out whether acupuncture is more effective for this condition. We will then run another comparison between the pooled acupuncture groups and sham acupuncture group to find out whether acupuncture is more efficacious. Finally, a comparison between acupuncture groups will be run to see if selecting points along meridians was a better treatment option. The above analysis will be performed using the ANCOVA model. Multiple comparisons will be adjusted according to the Bonferroni correction method.

The repeated measures analysis will be used in the different time point assessments for the secondary outcomes. The Kruskal-Wallis test will be employed in the analysis of skewed distribution data. There is a designated acupuncturist in each center to all the acupuncture treatment, which probably introduces clustering effect in this trial. Therefore, we calculated the intra-cluster correlation coefficient from the results of this trial and report the coefficient.

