## Discussion

Acupoints are the regions where qi and blood from the viscera and meridians effuse and infuse beneath the body surface; the meridians and collaterals internally pertain to viscera and externally connect with the extremities. Therefore, stimulating the acupoints on the affected meridians can produce specific effects on regulating the corresponding organs, and the specificity of acupoint effect is the important basis for this regulation effect [27,28]. However, the specificity of acupoint effect on the affected meridians, continues to be a conflicting theoratical issue in acupuncture field [29,30]. In recent years, much research on acupoint specificity has been launched, but the resultsare still inconclusive. There is a small sample study of 41 randomized hypertensive patients into two groups (one gave verum acupuncture, and the other received non-penetrating sham acupuncture). After 17 treatment sessions, the verum acupuncture group showed a significant decrease in blood pressure [31]. Similar results had been found in another study, which discovered that unlike sham acupuncture, after 6weeks of treatment with acupuncture according to TCM, the verum acupuncture significantly decreased mean 24-h ambulatory blood pressure [26]. On the other hand, another study of a higher quality obtained negative results on comparing active acupuncture with invasive sham acupuncture. They founded that active acupuncture provided no greater benefit than invasive sham acupuncture in reducing SBP or DBP [32].

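### The sample size cites a verum–sham difference of 7 mmHg but plans, without explanation, on 8 to 9 mmHg, and the unqualified 90% power is not supported at either the cited or the planned pooled contrast

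*Protocol article*

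**What the plan says.** The Protocol article, section Sample size calculation and statistical analysis, opens with one source for 24-h SBP. In it, "the average 24-hSBP of hypertensive patients rose 1.6 mmHg after being treated by sham acupuncture". For its verum arm it reports that "the average 24-hSBP of hypertensive patients lowered 5.4 mmHg after being treated with verum acupuncture", and so "the adjusted mean difference between the two groups was 7 mmHg".

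The next sentence sets the planning values: "In this study, we anticipated an 12 mmHg improvement by affected meridian acupuncture; 10 mmHg by non-affected meridian acupuncture; 3 mmHg by sham acupuncture". The fourth arm is put at "0 mmHg in the waiting-list group". Then: "The standard deviation is set as 20". The result is 93 per group for 90% power at a 5% level, raised to 107 per group (428 in total) for 15% drop-out. Nothing links the two sets of figures. The paragraph names neither the comparison, the test nor the sidedness behind 93, and does not say whether the SD is for levels or for changes.

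The same section plans three primary comparisons by ANCOVA with Bonferroni adjustment: pooled acupuncture against waiting list, pooled acupuncture against sham, and a comparison between acupuncture groups. The Discussion describes comparisons of the affected-meridian arm alone.

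**The concern.** The paragraph presents its evidence and then sizes the trial on something else. Because it begins with the earlier trial, a reader will naturally take the 90% as applying to a 7 mmHg difference from sham. The planning means imply a larger difference, and no reason is given, such as a minimum important difference, pilot data or a second source.

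The interpretation of a null result is at stake. If the sham comparison is non-significant and the report says the trial had 90% power, readers may conclude that a difference of the size in the cited trial has been ruled out. That would go beyond what this design supports.

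**Working it through.** **Inputs.** Cited difference: 5.4 + 1.6 = 7.0 mmHg, as stated. Planning means 12, 10, 3, 0; SD 20; 93 evaluable or 107 enrolled per arm; 1:1:1:1 allocation (Randomization section). Assumptions: two-sided tests; 0.05/3 = 0.0167 as the Bonferroni level for the three comparisons described.

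**Planned contrasts with sham.** Affected-meridian: 12 − 3 = 9. Non-affected: 10 − 3 = 7. Both verum arms pooled: (12 + 10)/2 − 3 = 8.

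**Can the plan's 93 be reproduced?** Use the normal approximation with (1.960 + 1.282)² = 10.507 and SD² = 400.
- Pooled verum v sham, 8 mmHg, 2:1: 1.5 × 400 × 10.507 / 64 = 98.5, so 99 per group.
- Affected-meridian v sham, 9 mmHg, 1:1: 2 × 400 × 10.507 / 81 = 103.8, so 104 per group.
- Four-group ANOVA on 12, 10, 3, 0: 60 per group.

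None gives 93. The 107 is 93 × 1.15 = 106.95.

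**Power with the plan's SD and n.** The standard error is 20 × √(1/n₁ + 1/n₂), and power comes from the non-central t with noncentrality difference/SE.
- Pooled, 186 v 93: SE = 20 × √(1/186 + 1/93) = 2.54.
- One verum arm, 93 v 93: SE = 20 × √(2/93) = 2.93.

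| Contrast with sham | Difference | Noncentrality | Power at 0.05 | Power at 0.05/3 |
|---|---|---|---|---|
| Pooled | 7 (cited) | 2.76 | 78% | 64% |
| Pooled | 8 (plan) | 3.15 | 88% | 77% |
| One verum arm | 7 (cited) | 2.39 | 66% | 49% |
| Affected-meridian arm | 9 (plan) | 3.07 | 86% | 74% |

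If all 107 per arm are analysed, pooled power at 7 mmHg is 84% at 5% and 71% at 0.05/3.

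**What would give 90% at 7 mmHg?** With 186 v 93 at unadjusted 5%, the effective SD must be about 17 (16.9). If 20 is the SD of levels and ANCOVA reduces it by √(1 − r²), then 20 × √(1 − 0.53²) = 16.96, so a baseline correlation of about 0.53 is needed. At r = 0.5 the effective SD is 17.3 and pooled power is 89% at 5%, but 78% at 0.05/3.

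**What a null result would show.** With SE 2.54 and t = 1.97, the 95% half-width is 5.0 mmHg. An observed difference of 3 mmHg would give about −2 to 8: non-significant, yet compatible with 7.

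**The case against.** The 90% is formally attached to the planning means, not to 7 mmHg, and sponsors may plan on an effect larger than one earlier trial found. A condensed article may also omit a rationale that the full protocol gives. This stands in part: the choice of target is a design judgement. It does not rescue the number, because at the plan's own pooled 8 mmHg, 93 per arm gives 88% before Bonferroni and 77% after, with no covariate gain.

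The departure on the comparison that matters is modest. A reader who sees verum roughly doubled and sham changing sign might infer a gross inflation of the effect. Those shifts largely cancel in the difference: 7 becomes 8 pooled, and the assumed non-affected-meridian v sham gap is exactly 7. The changed input costs about 10 percentage points (88% to 78%). The rest of the gap to 90% exists at the plan's own values.

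ANCOVA is planned and may recover most of the loss. This also stands, conditionally. The gain depends on a correlation the article does not give and on whether 20 is the SD of levels; if it is the SD of changes, the gain may be smaller.

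Two further inferences are tempting and unsupported. First, a reader might set the cited 5.4 mmHg fall against the plan's 0 for the waiting list and conclude that this comparison is badly underpowered at the cited effect. The cited trial, as reported here, gives no waiting-list change, so it provides no such effect. Second, a reader might infer from "another study of a higher quality obtained negative results on comparing active acupuncture with invasive sham acupuncture" that the plan's own evidence lies below 7 mmHg. The Discussion gives no effect size for that study, and beside it reports a positive trial in 41 patients, also without one.

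**Conclusion.** The point holds for the comparison with sham. The article moves without explanation from a cited 7 mmHg to a planned 8 mmHg pooled (9 for one arm), and its unqualified 90% is not supported at either pooled value with its own SD and n. Pooled power is about 78% at 7 mmHg and 88% at 8 mmHg at two-sided 5%, and about 64% and 77% at 0.05/3. For one verum arm against sham at 7 mmHg it is about 66% at 5%.

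These figures rest on SD 20 as the effective SD, 93 evaluable per arm, two-sided testing and three Bonferroni comparisons. It would go too far to say that 90% power at 7 mmHg is impossible: an effective SD of about 17 would give it for the pooled comparison at unadjusted 5%. The article does not state the assumptions needed to claim it. No shortfall against the waiting list at a cited effect has been shown.

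**What to change.** Keep enrolment as it is; the Trial status section reports 184 participants already recruited. Revise the sample-size paragraph to:

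1. Give the source for 12, 10 and 3 mmHg, or label them as optimistic targets that exceed the cited difference from sham.
2. Replace the unqualified 90% with the power of the planned pooled verum v sham comparison at both 7 and 8 mmHg, naming sidedness and the Bonferroni level. With no covariate gain these are about 78% and 88% at 5%, and 64% and 77% at 0.05/3.
3. State whether SD 20 is for levels or changes and what baseline correlation is assumed for ANCOVA. If a gain is claimed, recompute the powers in item 2 with the resulting effective SD.
4. State that a non-significant sham comparison will be read from its confidence interval and does not by itself exclude a 7 mmHg effect.

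The cost is wording and a short recalculation, with no extra patients. The downside is that the stated power becomes less favourable.
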